### Statistical analysis

The SUNRISE registry will be implemented in stages due to time and budget constraints. Aiming to initially gather data on acute ischemic stroke patients treated with SHX, describe and analyze the effects of SHX in real-world practice setting, and provide dependable data support for sample size calculation and protocol design in subsequent phases, the first phase is exploratory and has a target number of 1,000 participants. The next phases of this registry will be determined after the first phase of 1000 participants are completed. Baseline characteristics will be described using standard statistics. All baseline variables will be summarized using means and SDs for continuous variables that were normally distributed, while categorical variables were expressed as absolute frequencies and percentages. Given that the SUNRISE registry is one of the cohorts in the disease-specific CASES-TCM registry, a control group will be selected from the CASES-TCM population using a propensity score matching (PSM) approach to compare the effectiveness of SHX pill for acute ischemic stroke with those not receiving SHX treatment. The PSM will be performed with demographic and baseline characteristics. In each cohort, participants will be matched 1:1 based on propensity scores generated by logistic regression, using the nearest neighbor technique without replacement, with a maximum aperture of 0.2. After PSM, the comparability of outcomes between SUNRISE cohort and CASES-TCM cohort will be performed using a 2-sample t-test, one-way analysis of variance (ANOVA), or nonparametric tests (the $$\:{\chi\:}^{2}$$ test, Fisher’s exact test, or Mann-Whitney U test) as appropriate. Statistical analyses will be done using R software, version 4.1.2. Two-sided P values of less than 0.05 were accepted as statistically significant. A repeated measures analysis of variance (ANOVA) or mixed regression model will be used for repeated measurement data. To measure the relationships between multidimensional variables and outcomes of interest, multivariate regression analysis will be used in this study.

In addition, missing data are of great importance in real-world studies, in which missing data may cause seriously compromised inferences to scientific credibility of causal conclusion. Hence, we filled in the missing data using multiple imputations with predictive mean matching to ensure data integrity and comparability [31]. Moreover, in this real-world registry, potential confounding factors such as age, sex, smoking, body mass index, and severity of stroke, could be addressed in several ways [32]. The PSM approach will be used for the adjustment of measured confounders to ensure the balance between groups.

Pre-defined subgroup analyses will be performed of the effect of SHX at 3 months, subdivided by age, sex, severity of stroke, type of stroke, and TCM syndrome or TCM symptom.

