## Methods and design

### Study design

The SUNERISE registry is a multicenter, prospective, product-specific, observational study designed to provide insight into the administration of SHX pill for patients with AIS in the real-world clinical practice setting. Physicians decide whether to prescribe SHX pill based on their assessment of the patient’s overall condition, the drug’s stated indications, clinical guidelines, and the patient’s preferences. This present registry is one of the cohorts in the China Stroke Registry for Patients with Traditional Chinese Medicine (CASES-TCM), which is a prospective, multicenter, observational disease-specific registry [21]. Recruitment began on May 1, 2023, and the registry is scheduled to complete recruitment of all human participants by December 31, 2024. The SUNRISE registry has been approved by the Institutional Review Board of Dongzhimen Hospital, Beijing University of Chinese Medicine, Beijing, China (No. 2022DZMEC-268-02), as well as the local ethical committees of all participating sites.

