## Discussion

In the era of evidence-based medicine, RCTs and systematic reviews are the most reliable approaches to determine the efficacy and safety of treatment [33]. Doctors and patients mainly take into account relevant findings from RCTs and systematic reviews in making treatment decisions. However, there is a growing interest in whether the findings from RCTs can be reasonably applied to patients in a real-world clinical practice setting [34]. The external validity (or generalizability) of RCTs is sometimes poor, which could be mainly attributed to relatively strict inclusion and exclusion criteria. Usually, in well-controlled settings, RCTs set strict inclusion and exclusion criteria to ensure the homogeneity of target population, and eliminate potential bias by using blinded allocation, placebo control methods. These procedures increase the internal validity, but will inevitably lead to underestimation of the effectiveness of treatment in real-world clinical practice. On the contrary, patients in routine practice settings may often be older, with more complications. Hence, the promising results from real-world studies are not always consistent with those from RCTs. The real-world evidence is becoming more and more important in clinical practice because it can offer more insightful data on the long-term effectiveness and safety of treatments for patients receiving treatments in real-world clinical settings [35–37].

The SUNRISE registry is a multicenter, prospective, product-specific, observational study, which was designed as one of the intervention cohorts in the China Stroke Registry for Patients with Traditional Chinese Medicine (CASES-TCM) [21]. The CASES-TCM registry is a large-scale, prospective, multicenter, disease-specific, observational study, attempting to depict major clinical characteristics of stroke in patients treated with TCM and to explore the effectiveness in the comparison with different TCM medications, with an anticipated sample size of 20,000. Besides the SUNRISE registry, there are several ongoing real-world registries belonging to the cohorts of the CASES-TCM registry.

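### The described matching and tests name no hospital or enrolment-period term, so if SHX use is concentrated by hospital the SHX contrast may be biased and its standard error wrong

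*Protocol article*

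**What the plan says.** The Statistical analysis section of the protocol article states that "a control group will be selected from the CASES-TCM population using a propensity score matching (PSM) approach". The score comes from logistic regression, and "The PSM will be performed with demographic and baseline characteristics". Matching is 1:1, "using the nearest neighbor technique without replacement, with a maximum aperture of 0.2". The outcome comparison "will be performed using a 2-sample t-test, one-way analysis of variance (ANOVA), or nonparametric tests", with two-sided P below 0.05 as the criterion. The mixed model in that section is for repeated measurements. The multivariate regression lists no covariates and is not tied to the SHX contrast.

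On confounding, the same section says that "potential confounding factors such as age, sex, smoking, body mass index, and severity of stroke, could be addressed in several ways", and then "The PSM approach will be used for the adjustment of measured confounders to ensure the balance between groups". Every example named is a patient characteristic.

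Four other places bear on the point:

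- **Study design:** the study is multicentre, and "Physicians decide whether to prescribe SHX pill based on their assessment of the" patient's condition, together with indications, guidelines and preferences. SUNRISE recruits from 1 May 2023 to 31 December 2024.
- **Follow-up and study outcome:** local investigators at each site conduct the follow-up, in person or by telephone.
- **Discussion:** CASES-TCM anticipates 20,000 patients, and "there are several ongoing real-world registries belonging to the cohorts of the CASES-TCM registry".
- **Data collection and management:** baseline characteristics include GCS, NIHSS, mRS, BI and the TCM syndrome scale.

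**The concern.** When prescribing is discretionary, hospitals can differ in how often they use SHX. They can also differ in stroke care and in how their staff score the mRS. If the two patterns coincide, hospital becomes a confounder that patient-level matching does not remove: two patients with the same age, NIHSS and history still differ in where they were treated and who rated them. Nothing in the article confines controls to hospitals that also contribute SHX patients, or to the SUNRISE recruitment window.

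The second issue is variance. The listed tests treat all patients as independent. Patients from one hospital tend to resemble each other, and when the two groups draw on different hospitals this inflates the true variance of the difference.

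The first phase is exploratory, but the article intends it to support sample size and design of later phases. A difference driven by hospitals would carry forward.

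**Working it through.** **No stated figure to reproduce.** The 1,000 is set by time and budget, without event rate, effect size or power.

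**Inputs from the article:** 1,000 SHX patients; 1:1 matching, so at most 1,000 controls; two-sided 0.05.

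**Assumed, because the article does not give them:** 60% with mRS 0-2; ICC of 0.01 to 0.05; number of hospitals; share f of controls who come from SHX hospitals; difference D in outcome between SHX hospitals and the others.

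**Naive precision.** SE = sqrt(2 × 0.6 × 0.4 / 1,000) = 0.0219. The 95% half-width is 1.96 × 0.0219 = 4.3 points.

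**Effect of clustering.** Let a_j and b_j be the shares of the SHX and control groups in hospital j. Relative to a naive variance of 2/n, the true variance is (2/n)(1 − ICC) + ICC × Σ(a_j − b_j)². With R the ratio of true to naive SE, true type I error = 2 × (1 − Φ(1.96/R)). The 60% rate cancels here.

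*Disjoint hospitals.* The formula reduces to R = sqrt(1 + (m − 1) × ICC), where m is patients per hospital. For 20 hospitals per group (m = 50) and ICC 0.02: R = sqrt(1 + 49 × 0.02) = sqrt(1.98) = 1.41, and the error is 16.4%.

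| Hospitals per group | ICC 0.01 | ICC 0.02 | ICC 0.05 |
|---|---|---|---|
| 10 | 16.5% | 25.6% | 42.2% |
| 20 | 10.8% | 16.4% | 29.1% |
| 40 | 7.8% | 10.7% | 18.6% |

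*Partial overlap.* Take 20 SHX hospitals and 60 others, with patients spread evenly within each set. For f = 0.5: Σ(a_j − b_j)² = 20 × 0.025² + 60 × (0.5/60)² = 0.0125 + 0.0042 = 0.0167. At ICC 0.02 the variance is 0.00196 + 0.00033 = 0.00229, so R = sqrt(0.00229/0.002) = 1.07.

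| Share of controls from SHX hospitals | ICC 0.02 | ICC 0.05 |
|---|---|---|
| 0 | 12.7% | 22.6% |
| 0.25 | 9.2% | 15.4% |
| 0.5 | 6.7% | 9.4% |
| 0.75 | 5.2% | 5.6% |
| 1 (equal shares) | 4.8% | 4.4% |

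With equal shares in the same hospitals, R = sqrt(1 − ICC). ICC 0.01 then gives 4.9%, so the naive test is slightly conservative.

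**Bias.** For a given hospital difference, bias = D × (1 − f). With D = 5 points and no true SHX effect:

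- f = 0: bias 5.0 points; chance of a significant result with the naive SE 63%.
- f = 0.5: bias 2.5 points; chance 21%.
- Same hospitals in equal shares: no bias from hospital.

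The tables average over random hospital differences, whereas the bias figures fix one difference. They are two views of the same problem and should not be added together.

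**The case against.** This is a condensed article without its SAP, and a full covariate list is commonly left to that document. The confounder list is explicitly open-ended and the stated scope is measured confounders. SUNRISE is itself a cohort of CASES-TCM, so shared hospitals are plausible. All of this stands, and it rules out several stronger readings that a reader might infer:

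- **That matching uses patient characteristics only.** The article gives no closed list. What can be said is that hospital and enrolment period are not named, while the method and tests are specified.
- **That hospital differences will be read as an SHX effect.** This depends on how the two groups are spread over hospitals, which is not stated. The listed reasons for prescribing can vary within one hospital.
- **That intervals are too narrow.** The article specifies tests, not an interval, for this contrast. The direction depends on overlap and reverses slightly under equal shares. Unpaired tests on matched pairs also tend to be conservative.
- **That the groups differ in calendar period.** CASES-TCM dates are not given, so an imbalance is possible but not shown.
- **That GCS, BI and TCM syndrome are left out.** The Data collection section counts all three as baseline characteristics, so they already fall within the matching set.

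The objection does not dispose of the core. The article goes beyond a general promise of matching: it fixes the algorithm and names independent-sample tests. Followed as written, these neither compare patients within hospital nor allow for clustering.

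**Conclusion.** The point holds conditionally. The described match and tests have no hospital or enrolment-period term, in a setting where hospital could influence both treatment and the rated outcome. If SHX use is concentrated by hospital, the contrast may be biased and its standard error wrong.

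The size runs from negligible (type I error 4.4-4.9%, same hospitals in equal shares), through modest (6.7-9.4%, half of the controls from SHX hospitals), to serious (7.8-42.2%, disjoint hospitals). The range rests on the assumed ICC, hospital counts and overlap; the bias figures rest also on the assumed 60% rate and 5-point hospital difference. The documents do not show where in this range the study lies.

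**What to change.** In the Statistical analysis section:

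1. Match controls within hospital wherever non-SHX patients exist. Otherwise, let hospital, or hospital-level features if recorded, enter the propensity score. Where a hospital contributes only SHX patients, its indicator predicts treatment perfectly, so hospital-level features are the workable choice.
2. Restrict controls to the SUNRISE enrolment window, or include enrolment period in the score.
3. For the SHX contrast, replace the independent-sample tests with a hospital-clustered analysis: cluster-robust standard errors or a hospital random effect. Clustered standard errors repair the variance but not the confounding, so step 1 is still needed.
4. Report cross-hospital pairs and unmatched SHX patients separately.
5. Add reperfusion treatment to the score where it was given before SHX started and its timing is recorded. The Treatments section says that prescribed treatments are recorded, but does not say whether their order relative to SHX is.

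The change is mainly to analysis wording, provided that hospital and enrolment date can be linked for the CASES-TCM controls. The price is that some SHX patients will lack a within-hospital match; how many cannot be judged from the article. The interval may also widen: with 20 disjoint hospitals per group and ICC 0.02, the half-width goes from 4.3 to 6.0 points.

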## Discussion

In the era of evidence-based medicine, RCTs and systematic reviews are the most reliable approaches to determine the efficacy and safety of treatment [33]. Doctors and patients mainly take into account relevant findings from RCTs and systematic reviews in making treatment decisions. However, there is a growing interest in whether the findings from RCTs can be reasonably applied to patients in a real-world clinical practice setting [34]. The external validity (or generalizability) of RCTs is sometimes poor, which could be mainly attributed to relatively strict inclusion and exclusion criteria. Usually, in well-controlled settings, RCTs set strict inclusion and exclusion criteria to ensure the homogeneity of target population, and eliminate potential bias by using blinded allocation, placebo control methods. These procedures increase the internal validity, but will inevitably lead to underestimation of the effectiveness of treatment in real-world clinical practice. On the contrary, patients in routine practice settings may often be older, with more complications. Hence, the promising results from real-world studies are not always consistent with those from RCTs. The real-world evidence is becoming more and more important in clinical practice because it can offer more insightful data on the long-term effectiveness and safety of treatments for patients receiving treatments in real-world clinical settings [35–37].

The SUNRISE registry is a multicenter, prospective, product-specific, observational study, which was designed as one of the intervention cohorts in the China Stroke Registry for Patients with Traditional Chinese Medicine (CASES-TCM) [21]. The CASES-TCM registry is a large-scale, prospective, multicenter, disease-specific, observational study, attempting to depict major clinical characteristics of stroke in patients treated with TCM and to explore the effectiveness in the comparison with different TCM medications, with an anticipated sample size of 20,000. Besides the SUNRISE registry, there are several ongoing real-world registries belonging to the cohorts of the CASES-TCM registry.

There are several limitations in this study. First, a sample size of 1000 is relatively small for real-world registry. In the first phase of SUNRISE registry, 1000 patients will be enrolled initially, however, the subsequent phases of this registry will be determined after the first phase of 1000 participants are completed. Second, we only include patients with acute ischemic stroke, so we cannot investigate whether SHX is effective for intracerebral hemorrhage (ICH) in the current registry. In the subsequent phases of SUNRISE registry, both AIS and ICH patients will be included. And then, more findings could be established to understand the comprehensive benefits of SHX for acute stroke.

In addition to the primary analysis of the SUNRISE registry, several exploratory analyses could be done. First, the effectiveness and safety of SHX pill in the present real-world registry could be compared with the data from previous RCTs with PSM approach. Second, the characteristics of patients who present much greater response to SHX pill could be demonstrated in the current study, which will be undoubtedly helpful to guide the proper decision-making of SHX treatment, and enabling the personalized treatment. Third, the advantages of SHX pill for AIS could be summarized based on the data from the real-world setting, which may be helpful in the repositioning of SHX pill as a post-marketing drug. The findings of the SUNRISE registry will not only provide insights into the characteristics of patients who may benefit from SHX treatment, but also may enable the individualized treatment decision-making of SHX pill.

## Data Availability

No datasets were generated or analysed during the current study. All relevant data for this study will be made available from the corresponding author on reasonable request upon study completion.
